## Abstract

**Introduction:**

Compared with the traditional drug development pathway, investigating alternative uses for existing drugs (ie, drug repurposing) requires substantially less time, cost and resources. Immune checkpoint inhibitors are licensed for the treatment of certain breast, colorectal, head and neck, lung and melanoma cancers. These drugs target immune checkpoint proteins to reduce the suppression of T cell activation by cancer cells. As T cell suppression is a hallmark of cancer common across anatomical sites, we hypothesise that immune checkpoint inhibitors could be repurposed for the treatment of additional cancers beyond the ones already indicated.

**Methods and analysis:**

We will use two-sample Mendelian randomisation to investigate the effect of genetically proxied levels of protein targets of two immune checkpoint inhibitors—programmed cell death protein 1 and programmed death ligand 1—on survival of seven cancer types (breast, colorectal, head and neck, lung, melanoma, ovarian and prostate). Summary genetic association data will be obtained from prior genome-wide association studies of circulating protein levels and cancer survival in populations of European ancestry. Various sensitivity analyses will be performed to examine the robustness of findings to potential violations of Mendelian randomisation assumptions, collider bias and the impact of alternative genetic instrument construction strategies. The impact of treatment history and tumour stage on the findings will also be investigated using summary-level and individual-level genetic data where available.

**Ethics and dissemination:**

No separate ethics approval will be required for these analyses as we will be using data from previously published genome-wide association studies which individually gained ethical approval and participant consent. Results from analyses will be submitted as an open-access peer-reviewed publication and statistical code will be made freely available on the completion of the analysis.

STRENGTHS AND LIMITATIONS OF THIS STUDYAs germline genetic variants proxying circulating protein levels are randomly assorted at meiosis and fixed at conception, Mendelian randomisation analyses examining the effect of these proteins on cancer survival should be less prone to conventional issues of confounding and cannot be influenced by reverse causation bias.The use of a two-sample Mendelian randomisation framework will permit us to leverage large-scale genetic association data from separate samples, thus enhancing statistical power and precision of estimates.The generalisability of our findings to populations of non-European ancestry may be unclear.Mendelian randomisation analysis can only evaluate the on-target effects of immune checkpoint inhibitors.Sample sizes of genome-wide association studies of cancer survival are low in comparison to cancer risk, which will limit the statistical power of our analyses.

## Introduction

Drug repurposing is the use of approved drugs for another indication.^1 2^ The traditional development and testing pathway of candidate drugs is expensive and time-consuming, with an estimated cost of US$2–3 billion and 13 years of research on average required for a chemical compound to be approved for use in clinical practice.^3^ In contrast, drugs that are tested for a repurposed use should already have demonstrated success in phase I trials for their original indication and thus their safety profiles for human use are known.^3–6^ Consequently, clinical testing for a repurposed use of a drug can begin at phase II trials, reducing associated time and resource requirements.^3–6^

Despite advances in screening and treatment strategies, the number of people diagnosed with, and dying from cancer, continues to increase. Globally, there were estimated to be 19.3 million new cancer diagnoses and 10.0 million cancer deaths in 2020.^7^ Seven cancer sites (breast, colorectal, head and neck, lung, melanoma skin, ovarian and prostate cancer) were estimated to contribute to 48% of the incidence and 45% of mortality from all cancer sites globally in 2020.^7^ In addition to the high burden of cancer, there are issues associated with currently available treatments such as development of resistance, severity of side effects and lack of efficacy in some individuals.^8^ Identifying new strategies for the treatment of these high-burden cancers using drug repurposing could minimise the cost and patient involvement required for the assessment of their efficacy. Several drugs have been successfully repurposed for cancer treatment, including non-cancer drugs such as thalidomide which was originally developed to treat morning sickness in pregnancy but is now approved to treat multiple myeloma.^3 8 9^

Shared hallmarks of cancer common to different cancer sites represent an opportunity for drug repurposing using approved drugs which target these mechanisms across multiple sites.^3^ One such hallmark is the avoidance of immune destruction, which can be suppressed using immune checkpoint inhibitors.^3 10 11^ The first immune checkpoint inhibitor approved by the US Food and Drug Administration was the anti-cytotoxic T-lymphocyte associated protein 4 monoclonal antibody, ipilimumab, for the treatment of melanoma in 2011.^10^ Following the approval of ipilimumab, several other immune checkpoint inhibitors have also been approved for a range of cancer indications.

Two examples of immune checkpoint proteins which have been successfully targeted in cancer treatment are programmed cell death protein 1 (PD-1) and programmed cell death ligand 1 (PD-L1).^10^ The anti-PD-1 monoclonal antibodies include cemiplimab (Libtayo), dostarlimab (Jemperli), nivolumab (Opdivo) and pembrolizumab (Keytruda), and the anti-PD-L1 monoclonal antibodies include atezolizumab (Tecentriq), avelumab (Bavencio) and durvalumab (Imfinzi).^10 12^ These seven immune checkpoint inhibitors have been approved by the Medicines and Healthcare products Regulatory Agency (MHRA) for specific cancer indications, including some indications for the seven cancer types detailed previously (table 1, online supplemental table 1). Across anti-PD-1 immune checkpoint inhibitors, there are approved indications for the treatment of breast, colorectal, head and neck, and lung cancers and melanoma, while anti-PD-L1 immune checkpoint inhibitors have been approved for breast and lung cancer treatment^13–19^ (table 1, online supplemental table 1).

10.1136/bmjopen-2023-075981.supp1Supplementary data

**Table 1 T1:** Medicines and Healthcare products Regulatory Agency (MHRA) indications of anti-programmed cell death protein 1 (PD-1) and anti-programmed cell death ligand 1 (PD-L1) monoclonal antibodies, obtained 25 March 2023

Protein target	Immune checkpoint inhibitor	Cancer						
		Breast	Colorectal	Head and neck	Lung	Melanoma	Ovarian	Prostate
PD-1	Cemiplimab^13^	–	–	–	A	–	–	–
	Dostarlimab^14^	–	–	–	–	–	–	–
	Nivolumab^15^	–	A	A	A	A	–	–
	Pembrolizumab^16^	A	A	A	A	A	–	–
PD-L1	Atezolizumab^17^	A	–	–	A	–	–	–
	Avelumab^18^	–	–	–	–	–	–	–
	Durvalumab^19^	–	–	–	A	–	–	–

‘A’ represents immune checkpoint inhibitors with at least one approved indication for the cancer type either as monotherapy or as part of combination therapy.

The approvals for anti-PD-1 and anti-PD-L1 immune checkpoint inhibitors are not uniform across cancer sites, even for the drugs targeting the same immune checkpoint protein (table 1). However, this may be explained by an absence, rather than failure, of comparable clinical trials for certain drugs within these drug target categories. For example, pembrolizumab is the only anti-PD-1 immune checkpoint inhibitor approved for a breast cancer indication by the MHRA^16^ (table 1), likely due to lack of complete late-stage clinical trials with large sample sizes investigating the efficacy of the other three anti-PD-1 immune checkpoint inhibitors.^20 21^ Similarly, although nivolumab and pembrolizumab both have colorectal cancer indications, there are differences in the characteristics of the patient populations these drugs are approved to treat^15 16^ (table 1, online supplemental table 1). Nivolumab is approved to treat patients with mismatch repair deficient (dMMR) or microsatellite instability high (MSI-H) colorectal cancer after chemotherapy as part of a combination therapy with ipilimumab^15^ (online supplemental table 1). In contrast, pembrolizumab as monotherapy is approved to treat metastatic or unresectable dMMR/MSI-H colorectal cancer, the latter following previous treatment^16^ (online supplemental table 1).

The approved indications of these immune checkpoint inhibitors are highly specific in many cases, particularly with respect to molecular tumour markers and treatment history. For example, durvalumab has been approved by the MHRA for the treatment of adult patients with locally advanced, unresectable non-small cell lung cancer if at least 1% of their tumour cells express PD-L1 and their disease did not advance after previous platinum-based chemoradiotherapy^19^ (online supplemental table 1). The populations in clinical trials tend to be selected based on prior evidence of antiproliferative or anti-tumour responses and favourable pharmacodynamics and pharmacokinetics in preclinical studies and early-stage trials.^22^ For example, trials investigating the efficacy of anti-PD-L1 immune checkpoint inhibitors for ovarian cancer treatment have largely been restricted to evaluating patients with treatment-naïve advanced stage (stage III–IV) epithelial ovarian cancer, but have not been successful^23–27^ (table 1, online supplemental table 1).

The interaction between PD-L1 on the surface of cancer cells and PD-1 on the surface of activated T cells suppresses further T cell activation.^10 20 21 28^ Therefore, PD-1 and PD-L1 inhibitors suppress this interaction and so support T cell activation during anti-cancer immune responses.^10 12^ While PD-1 is largely expressed on immune cells, PD-L1 is expressed on a wider variety of non-haematopoietic cells, including tumour cells.^29–32^ Although there is uncertainty over the prognostic value of blood-based measures, previous studies have found that higher circulating (ie, blood-based) PD-1 and PD-L1 levels are associated with poorer prognosis for patients diagnosed with cancer at different anatomical sites. For example, higher plasma soluble PD-1 and PD-L1 expression levels were associated with decreased progression-free survival for patients with advanced-stage high-grade serous ovarian cancer compared with those with lower PD-1 and PD-L1 expression.^33^ However, when accounting for other clinical factors in multivariable analyses, only soluble PD-L1 expression levels remained associated with progression-free survival for these patients.^33^ Higher circulating soluble PD-L1 expression was also associated with decreased overall and progression-free survival in a meta-analysis of patients with cancer at different anatomical sites, including non-small cell lung cancer and melanoma patients who had been treated with immunotherapy.^34^ In contrast, although low serum exosomal PD-L1 expression was associated with increased median overall survival for pancreatic ductal adenocarcinoma patients compared with those with high exosomal PD-L1 expression, there was little statistical evidence to support this observed difference.^35^ Therefore, even though the prognostic roles of circulating PD-1 and PD-L1 expression levels have not been fully determined, there is some evidence supporting an association between blood-based measures of these immune checkpoint proteins and cancer survival, and the mechanism of action of these drugs is mediated by T cells.^33–35^

### Mendelian randomisation

Mendelian randomisation (MR) investigates the association between an exposure and outcome using genetic variants associated with the exposure as a proxy for the exposure of interest.^1^ Two-sample MR uses measurements of genetic variant-exposure and genetic variant-outcome associations from separate studies, permitting analyses to leverage large-scale genetic association data for protein measures and cancer survival.^36 37^

MR should be less vulnerable to conventional issues of confounding, as genetic germline variants are randomly assorted at meiosis.^5 36–42^ As germline genetic variants are fixed and cannot be influenced by subsequent disease status, MR analyses are immune to reverse causation bias.^5 36–40^ Since MR analyses often use existing genetic association data, causal relationships can be tested in a more cost-effective and time-efficient manner than in randomised controlled trials.^1 36–38 40^

### Aims

The aim of this study is to investigate the association between genetically proxied circulating PD-1 and PD-L1 protein levels and survival of seven cancer types (breast, colorectal, head and neck, lung, melanoma, ovarian and prostate). These seven cancer sites have been chosen for inclusion as they have the most well-powered and accessible genome-wide association study (GWAS) survival data and make an important contribution to the overall global cancer burden.

These analyses will enable us to evaluate the repurposing potential of PD-1 and PD-L1 to new cancer indications. This will include potential repurposing to cancers without any existing approvals, as well as repurposing to new patient populations for cancers with some existing approvals. Previous MR studies have focused almost exclusively on causes of cancer risk. By including cancers with approved indications for PD-1 and PD-L1 inhibitors, which serves as a positive control, our analyses will also provide insight into the applicability of MR to studies of cancer survival.

## Methods and analysis

### Exposures

Rather than investigating the efficacy of specific immune checkpoint inhibitor compounds, their on-target effects will be proxied using genetic instruments which represent decreased circulating levels of their protein targets, PD-1 and PD-L1. Since our primary instruments will be based on studies in blood, we anticipate that our analyses may not fully proxy the mechanism of PD-1 and PD-L1 inhibitors in all biologically relevant tissues, an issue we will address in instrument validation analyses (see below).

Single-nucleotide polymorphisms (SNPs) associated with circulating PD-1 or PD-L1 expression levels will be used to proxy expression of these proteins. These genetic instruments will be selected from a GWAS of circulating proteins in 54 219 participants of majority European ancestry in the UK Biobank cohort.^43^ Statistical analysis, imputation, quality control and protein expression quantification in this study have been described previously.^43^

### Outcomes

Genetic association data will be obtained from GWAS of cancer survival in individuals of European ancestry with breast,^44^ colorectal,^45^ head and neck (unpublished), lung (unpublished), melanoma,^46^ ovarian^47^ and prostate cancer.^47^ The outcome in each GWAS was defined as cancer-specific mortality, except for the lung and head and neck cancer GWAS which defined the outcomes as all-cause mortality, and the ovarian cancer GWAS which examined both progression-free survival and overall survival (all-cause) as outcomes.^44–48^ To increase statistical power, we will combine the consortium site-specific GWAS with additional studies of cancer survival in Genomics England (unpublished) (table 2).

**Table 2 T2:** Number of patients and mortality events occurring in the site-specific consortium genome-wide association study (GWAS) and Genomics England GWAS for each cancer site

Cancer site	Number of patients			Number of events		
	Consortium GWAS	Genomics England	Total	Consortium GWAS	Genomics England	Total
Breast	91 686^44^	2183	93 869	7531^44^	238	7769
Colorectal	16 964^45^	2190	19 154	4010^45^	541	4551
Head and neck	10 000‡ (unpublished)	196	10 196	3300 (unpublished)	74	3374
Lung	7352 (unpublished)	1318	8670	4598 (unpublished)	592	5190
Melanoma	10 982^46^	219	11 201	1041^46^	108	1149
Ovarian	2901^47^	494	3395	1656*	217	1873
Prostate	24 023^48^	–†	24 023	3513^48^	–†	3513

The head and neck, lung and ovarian cancer mortality events are from all causes, while the mortality events for the other cancer sites are cancer site specific.

*The number of mortality events in the ovarian cancer GWAS was estimated based on the death proportion of 11 Ovarian Cancer Association Consortium (OCAC) studies (AUS, BAV, BEL, HAW, HSK, MAC, MAL, MAY, NCO, NEC, PVD) (0.571)^70^ and the ovarian cancer GWAS sample size (2901).^47^

†There were fewer than 50 patients with prostate cancer included in the Genomics England survival GWAS so these will not be combined with the consortium site-specific prostate cancer GWAS.

‡The number of head and neck cancer cases in the consortium GWAS is an approximate estimate.

### Data harmonisation

Harmonisation of genetic data is the process by which the exposure and outcome GWAS summary statistics are joined together and oriented to reflect the same effect alleles. Therefore, harmonised data will only include SNPs which were common to both the protein expression and respective cancer survival GWAS.

Harmonisation will be performed using the harmonise_data function from the TwoSampleMR R package (https://mrcieu.github.io/TwoSampleMR/).^49 50^ This will use the function’s default option which infers the positive strand using allele frequencies for palindromic SNPs (https://mrcieu.github.io/TwoSampleMR/).^49 50^ The correlation between exposure and outcome GWAS SNP effect allele frequencies will be compared following data harmonisation. If data harmonisation has been successful, the correlation coefficient would be expected to be close to 1, as this would suggest that the same alleles have been chosen as the effect allele in both GWAS summary statistic datasets.

### Mendelian randomisation

#### Assumptions

There are three key assumptions of MR: relevance, exchangeability and exclusion restriction.^39 42^ The relevance assumption states that the genetic instrument must be associated with the exposure of interest, for example, in this study the circulating levels of the drugs’ protein target.^36 42^ The second MR assumption, exchangeability, requires there are no common causes of the instrument and outcome.^36 42^ The final MR assumption, exclusion restriction, states that there must be no horizontal pleiotropy.^36 38–41 51^ Horizontal pleiotropy occurs when there are additional pathways between the instruments and outcome, independent of the exposure.^36 42 51^

#### Genetic instrument selection

The UK Biobank protein expression GWAS summary statistics^43^ will be used to select SNPs associated with circulating PD-1 or PD-L1 concentration. The genomic regions of the genes encoding PD-1 (*PDCD1*, chr2:241849884–241858894 in human genome build 38 (hg38)) and PD-L1 (*CD274*, chr9:5450503-5470566 in hg38) will be used to define *cis* and *trans* genetic instruments based on different window sizes.

To minimise vulnerability to horizontal pleiotropy, only SNPs within and in proximity to the gene encoding the target protein, known as *cis* SNPs, will be included in genetic instrument sets for the main analyses.^51^
*Cis* instruments to proxy both proteins will be constructed in PLINK version 1.9^52 53^ using SNPs in or within 500 kilobases (kb) from *PDCD1* or *CD274* that are associated with expression of these proteins (p < 5×10^-6^) at linkage disequilibrium (LD) r^2^ < 0.30 (based on clumping with a random sample of 10 000 European participants from the UK Biobank).^5 51 54^

#### Estimator

Where the genetic instrument consists of one SNP, the Wald ratio will be used to assess the association between a protein instrumented by this SNP and cancer survival.^6 40 55^ Where a genetic instrument consists of two or more SNPs, the inverse-variance weighted method will instead be used to investigate the association between a protein instrumented by these SNPs and cancer survival.^6 40 55^ Any LD between SNPs included in an instrument will be accounted for in analysis using a SNP correlation matrix based on a random sample of 10 000 participants of European ancestry from the UK Biobank.^42 54 56^ Heterogeneity of MR results across independent SNPs included in the genetic instrument sets will be assessed using Cochran’s Q tests and MR results will be compared across each SNP in the instrument by visual inspection.^36 40 57^

The protein expression GWAS included age, age², sex, age–sex interaction terms, protein expression level measurement batch, UK Biobank centre, genotyping array, the first 20 principal components (PCs) of genetic ancestry, and duration between blood sample collection and protein expression measurement as covariates, in addition to preselection status of the participants for the replication cohort.^43^

Aside from the breast cancer GWAS which did not adjust for any covariates, the cancer site-specific GWAS were all adjusted for genetic PCs (although for different numbers of PCs).^44–48^ The colorectal cancer survival GWAS additionally adjusted for age at diagnosis, sex, genotyping platform and study where the data originated from.^45^ The head and neck cancer GWAS will be additionally adjusted for age, sex, stage at diagnosis (stratified as early or late stage) and cancer subtype. The lung cancer survival GWAS also adjusted for age and sex, and separated participants into early-stage (stage I–II), late-stage (stage III–IV) and all stage analyses (unpublished). The melanoma survival GWAS included age and sex as covariates in addition to genotyping batch for one cohort.^46^ For the ovarian cancer survival GWAS, the primary study, residual disease, tumour stage, histology, tumour grade and age were also adjusted for.^47^ The prostate cancer survival GWAS additionally included age, diagnostic prostate-specific antigen level and Gleason score as covariates.^48^

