#### Power

Using the UK Biobank protein expression GWAS,^43^ the lead *cis* SNP for *PDCD1* (variant located at chr2:242801752 in human genome build 37 (hg37) with CG (A0) and C (A1) alleles) explained approximately 2.97% of the variation in circulating PD-1 expression level while the lead *cis* SNP for *CD274* (rs822341) explained approximately 4.17% of the variation in PD-L1 expression level.

Across all seven cancer types, there is an estimated power of 80% to detect HRs of at least ≥1.63 or ≤ 0.62 per unit decrease in normalised protein expression levels (alpha set to 5%) (table 3).

**Table 3 T3:** Estimated number of participants (N), death proportion, median survival, and HR per SD decrease detectable with 80% power for each cancer site

Cancer	N	Death proportion	Median survival (months)	HRs detectable at estimated 80% power	
				PD-1	PD-L1
Breast	93 869	0.083	64.8^71^	HR ≥ 1.21 HR ≤ 0.83	HR ≥ 1.17 HR ≤ 0.86
Colorectal	19 154	0.238	38.4^71^	HR ≥ 1.28 HR ≤ 0.78	HR ≥ 1.22 HR ≤ 0.82
Head and neck	10 196	0.331*	54.3^72^	HR ≥ 1.34 HR ≤ 0.75	HR ≥ 1.26 HR ≤ 0.79
Lung	8670	0.599*	3.6^71^	HR ≥ 1.27 HR ≤ 0.79	HR ≥ 1.21 HR ≤ 0.83
Melanoma	11 201	0.103	53.4^73^	HR ≥ 1.63 HR ≤ 0.62	HR ≥ 1.50 HR ≤ 0.67
Ovarian	3395	0.552*	30.1^74^	HR ≥ 1.48 HR ≤ 0.68	HR ≥ 1.37 HR ≤ 0.73
Prostate	24 023	0.146	62.4^71^	HR ≥ 1.33 HR ≤ 0.75	HR ≥ 1.26 HR ≤ 0.79

HRs per standard deviation (SD) decrease estimated to be detected at 80% power calculated with the survSNP R package^75^ (https://cran.r-project.org/web/packages/survSNP/index.html) using the combined estimated sample size and death proportion from each cancer survival genome-wide association study (GWAS) and the respective Genomics England cancer survival GWAS, median survival and assuming a false positive rate of 0.05. Death proportion was defined as the proportion of cancer cases who died due to all-cause or cancer-specific mortality. Transformation of protein level measurements into normalised protein expression (NPX) units on a log₂ scale have been described previously.^43^

*Death proportion due to all-cause mortality.

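### The breast cancer survival GWAS enters the main Mendelian randomisation (MR) analysis without ancestry adjustment, and no planned analysis checks for population structure

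*Protocol article*

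**What the plan says.** The Estimator section of the protocol article lists the covariates of each input GWAS. For the outcomes it says: "Aside from the breast cancer GWAS which did not adjust for any covariates, the cancer site-specific GWAS were all adjusted for genetic PCs". The colorectal GWAS was also "additionally adjusted for age at diagnosis, sex, genotyping platform and study where the data originated from", and the ovarian GWAS lists the primary study among its covariates. On the exposure side, the protein GWAS included 20 PCs.

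Under Assumptions, the article says: "The second MR assumption, exchangeability, requires there are no common causes of the instrument and outcome".

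Under Outcomes, the article says that "we will combine the consortium site-specific GWAS with additional studies of cancer survival in Genomics England". For breast (Table 2), the consortium gives 91 686 patients and 7531 deaths, and Genomics England gives 2183 patients and 238 deaths. The covariates of the Genomics England analyses are not stated. All outcome data are restricted to European ancestry.

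The Positive controls section names breast as one of five positive-control sites and calls these controls crude. Table 3 gives breast the smallest detectable hazard ratios: 1.21 or 0.83 for PD-1 and 1.17 or 0.86 for PD-L1.

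**The concern.** Ancestry is the usual common cause of a genotype and a disease outcome, and PCs are the usual control for it. The plan reports that one of its outcome datasets lacks this control, but it neither replaces the estimates nor adds a check. The planned analyses have other targets:

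- The allele-frequency correlation under Data harmonisation checks allele coding.
- The SNP correlation matrix handles linkage disequilibrium.
- The Sensitivity analyses section covers instrument thresholds, *trans* variants, leave-one-SNP-out, colocalisation, phenome-wide look-up and index event bias.

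None of these addresses population structure in the breast data.

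Breast is where a small bias would be most visible, because it has the most events. With lung, it is also one of only two sites in Table 1 with approved inhibitors of both targets. A spurious breast result in either direction could be read as evidence for or against the instruments.

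**Working it through.** **1. The plan's own figures.** I used ln HR = (1.960 + 0.842)/√(events × R²), with 7769 events (Table 2), R² of 0.0297 and 0.0417 (Power section) and two-sided alpha 0.05. The article says only "assuming a false positive rate of 0.05", without stating sidedness.

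- PD-1: 2.802/√(7769 × 0.0297) = 2.802/15.19 = 0.184, so HR 1.203 or 0.832. Table 3 has 1.21 or 0.83.
- PD-L1: 2.802/√(7769 × 0.0417) = 2.802/18.00 = 0.156, so HR 1.168 or 0.856. Table 3 has 1.17 or 0.86.

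Table 3 is reproduced to within 0.01. It assumes a test of correct size, so no residual structure.

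**2. Share of unadjusted data.** Genomics England supplies 238/7769 = 3.1% of breast deaths and 2183/93 869 = 2.3% of patients. Whatever its covariates, it cannot dilute a problem in the consortium data.

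**3. When an unadjusted test goes wrong.** Take K equal studies of m = 91 686/K patients, with allele-frequency differentiation Fst between studies, intraclass correlation ICC for death, and no SNP effect within any study. The variance of the pooled score is then inflated by about

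1 + 2 × m × ICC × Fst × (K − 1)/K.

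The excess is a product. If either Fst or ICC is zero there is none, so shared mortality within studies is not enough. K, Fst and ICC are not in the documents and are assumptions here. The type I error is 2 × (1 − Φ(1.96/√inflation)).

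| Studies | Fst | ICC | Inflation | Type I error, formula | Type I error, simulated |
|---|---|---|---|---|---|
| 20 | 0.001 | 0.005 | 1.04 | 5.5% | 5.7% |
| 20 | 0.001 | 0.02 | 1.17 | 7.1% | 6.9% |
| 20 | 0.001 | 0.05 | 1.44 | 10.2% | 10.0% |
| 80 | 0.0005 | 0.05 | 1.06 | 5.7% | 5.7% |

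For example, row 3 is 1 + 2 × 4584 × 0.05 × 0.001 × 0.95 = 1.44. The most extreme setting tried (10 studies, Fst 0.004, ICC 0.05) simulated at 31.6%.

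A second simulation (2000 replicates per setting) varied the standard deviation (SD) of the log hazard between studies. With 20 studies:

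- Fst 0.002, SD 0.2: 4.9%
- Fst 0.002, SD 0.5: 10.4%
- Fst 0.005, SD 0.2: 7.9%
- Fst 0.005, SD 0.5: 15.6%

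With 80 studies, Fst 0.005 and SD 0.5 it was 7.6%. At Fst 0.0005 no excess was visible. A study-stratified test stayed at 4.2-6.2% throughout, which is nominal within simulation error.

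**4. By inflation factor.** An assumed genomic inflation of 1.02, 1.05, 1.10 or 1.20 gives a type I error of 5.2%, 5.6%, 6.2% or 7.4%.

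**5. By bias at one locus.** With 7769 events, a bias b in log HR per genotype SD shifts the test statistic by b√7769. An assumed b of 0.002 gives a shift of 0.18 and a type I error of 5.4%. For b = 0.01 the shift is 0.88 and the error 14.3%. The ratio estimator multiplies such a bias by 1/√0.0297 = 5.8 (PD-1) or 1/√0.0417 = 4.9 (PD-L1). A bias of 0.01 therefore becomes about 0.06 or 0.05 in log HR per SD of protein.

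**The case against.** The strongest reply is that this is a disclosed feature of an inherited dataset, already restricted to European ancestry. The sentence about covariates also does not settle how study was handled. Stratifying the baseline hazard by study or country, or meta-analysing study results, is not covariate adjustment, and either would remove between-study confounding. That reply stands against several stronger readings that a reader might infer:

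- **That contributing study was ignored and clustered patients were treated as independent.** The article does not say so. Clustering in survival alone would not inflate a SNP test anyway (step 3). The risk is confounding by ancestry, and what is certain is the absence of PCs.
- **That the breast test has an error rate of about 10%.** The ICC of 0.05 behind the 10.0% figure implies that 90% of studies have death proportions between about 1.1% and 20%, which is implausibly wide. The first simulation also used a binary death indicator, so differences due only to follow-up length would count as differences in hazard.
- **That Table 3 needs restating now.** Any inflation factor chosen today would be an assumption.
- **That Genomics England can serve as a check.** Its covariates are not stated. With 238 deaths its detectable HR is about 2.87 (PD-1) or 2.43 (PD-L1), by the formula in step 1, so agreement in direction would say little.
- **That breast cannot be compared with the other sites for this reason.** The sites already differ in endpoint and covariates, and the plan does not pool them.

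Breast is also only one of five positive controls that the article itself calls crude. None of this answers the remaining point: the plan names an unadjusted input, states an assumption that this input may violate, and includes no check.

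**Conclusion.** The point holds in a limited form. The missing ancestry adjustment for breast and the lack of any analysis of population structure follow directly from the article. That this can push the error rate above 5% follows from the calculation, but the size cannot be derived from the documents. Under the assumptions shown, there is no visible excess with low Fst, modest differences in baseline hazard, or stratification by study. The rate reaches about 7-10%, and more in the extreme settings, only if allele frequency and hazard both differ substantially between studies. This is a cheap improvement that could change the breast inference. It does not show that the breast result will be wrong.

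**What to change.** In the Estimator section:

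1. State whether the breast GWAS was stratified or meta-analysed by study or country.
2. Compute the LD-score regression intercept, or the genomic inflation factor, from the full breast summary statistics. Report it and, if it is above 1, multiply the breast standard errors by its square root in the MR.
3. Ask the consortium for PC-adjusted, study- or country-stratified estimates for the *PDCD1* and *CD274* instrument variants. Use them for the breast analysis, or at least as a sensitivity analysis.
4. If they cannot be had, label the breast result as not ancestry-adjusted, and note that scaling the standard errors does not remove bias specific to one locus.
5. Restate the breast row of Table 3 only if the observed inflation requires it.

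Cost: step 2 needs only summary statistics and adds little work. Step 3 depends on an outside group rerunning its models, so it is conditional. Breast intervals may widen slightly. As an illustration, an inflation of 1.10 widens them by √1.10 − 1 = 4.9%. It would move the detectable HR from 1.21 to exp(ln 1.21 × 1.049) = 1.22 for PD-1 and from 1.17 to 1.18 for PD-L1.
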